## **2.2 Study Objectives**

Primary:

- To investigate the use of  $^{18}\text{F}$  FDG-PET/MRI to estimate the biodistribution of *Plasmodium* species in human volunteer induced blood stage malaria studies.
- To investigate the use of  $^{18}\text{F}$  FDG-PET/MRI to estimate the biomass of *Plasmodium* species.
- To investigate the use of advanced dedicated MRI techniques to early *Plasmodium* infection.

Secondary:

- To describe the relative burden of organ-specific tissue sequestration in *Plasmodium* infection.
- To describe the impact of early malaria infection on glucose metabolism.
- To describe the MRI brain findings of early malaria infection in a prospective participant cohort.

### **i. Research Question**

The present EXPLORATORY STUDY has been designed to establish the role of  $^{18}\text{F}$  FDG-PET/MRI and advanced dedicated MRI techniques in studying the

pathophysiology of subpatent malaria following low dose *Plasmodium* exposure in healthy adults.

## **ii. Study Outcome Measures**

### **Primary**

The primary objective of the study is to assess the application of whole body  $^{18}\text{F}$  FDG-PET/MRI in describing the parasite biodistribution and biomass in subpatent malaria. This is a hypothesis generating pilot investigation expected to have predominately descriptive outcomes.

The primary outcome measures will be the quantified and semi-quantified  $^{18}\text{F}$  FDG uptake values from specific regions of interest. Regions of interest for quantification of uptake will be spleen, bone marrow (lumbar spine and/or pelvis), muscle bulk (quadriceps) and brain. Post inoculation measurements will be compared to baseline pre inoculation uptake values. Biochemical markers of parasitaemia and total biomass from MAIN study data will be compared to  $^{18}\text{F}$  FDG uptake values.

Any other regions of interest (as deemed by the investigators) identified after imaging will have semi-quantified  $^{18}\text{F}$  FDG uptake values calculated for further comparison.

The other primary objective seeks to apply advanced MRI techniques to early *Plasmodium* infection. This will generate descriptive outcomes and inform future MRI sequence selection to optimize imaging in malaria.

### **Secondary**

The relative burden of organ specific sequestration will be determined by comparing  $^{18}\text{F}$  FDG uptake values for each region of interest.

The impact of early malaria infection on glucose metabolism will be evaluated in assessing each of the above outcomes.

The MRI findings of early malaria will be presented in a descriptive manner, outlining any interval changes in high-resolution brain MRI for this prospective cohort.

## **iii. Study Rationale**

This EXPLORATORY STUDY has been designed to establish the role of  $^{18}\text{F}$  FDG-PET/MRI and advanced MRI techniques in studying the pathophysiology of subpatent malaria. The selection of this radiotracer and imaging modality offers a well-validated model for exploring nuclear medicine functional imaging of malaria infection in a healthy human volunteer population.

### **Hypotheses**

- Whole body  $^{18}\text{F}$  FDG-PET/MRI is a technically feasible imaging modality for the study of subpatent malaria infection.

- Quantitative and semi-quantitative uptake of  $^{18}\text{F}$  FDG is proportional to estimated parasite biomass and parasitaemia.
- Subtle changes in the vasculature of the brain are present and identifiable on MRI in subpatent malaria infection.

#### iv. Potential Risks and Benefits

##### Potential Risks

There is a small risk associated with radiation exposure from the radiotracer  $^{18}\text{F}$  FDG. This falls into the low risk category of the ARPANSA guidelines. This is outlined in the radiation assessment report (Appendix A). There is a small risk of perturbation in blood glucose levels following  $^{18}\text{F}$  FDG administration. To minimize this risk all participants will undergo blood glucose testing at screening and further testing prior to any administration if there are clinical concerns to ensure they are suitable to receive the radiotracer. There is a very small risk of a reaction to the infusion of the radiotracer  $^{18}\text{F}$  FDG. This is outlined in section 8.4. A product information sheet for  $^{18}\text{F}$  FDG will be provided to each participant (Appendix G.)

There is the risk of incidental abnormalities being identified on whole body PET/MRI imaging. These will be managed on an individual basis in consultation between the reporting radiologist, study doctor, principal investigator and participant.

Other risks, including those associated with IBSM inoculation and blood collection are as described in the MAIN study. EXPLORATORY STUDY involvement is not expected to alter these pre-existing risks.

##### Potential Benefits

There are no direct health benefits from participation in this EXPLORATORY STUDY.

Other potential benefits are as described in the MAIN study.

### **3. STUDY DESIGN**

This is an EXPLORATORY STUDY comprising a population recruited from single-center, IBSM model MAIN studies. The population will consist of up to eight healthy adults inoculated with *Plasmodium* species parasite from existing MAIN study population.

MAIN study refers to the parallel IBSM MAIN study from which the participant is drawn from.

Participants will receive **two** scans: the first within one week prior to MAIN study inoculation and the second one to two days prior to confinement with peak parasitaemia post BSP inoculation (estimated InD 6 to 7 for *P. falciparum* and InD 8 to 9 for *P. vivax*). Blood samples will be collected at MAIN study timepoints, with no

additional collections planned for the EXPLORATORY STUDY.

**Preparation:**

At screening, participants will be consented for EXPLORATORY STUDY inclusion. At the time of consent the participant and study doctor will complete the MRI checklist (see Appendix B) and education regarding pre-imaging preparation. In the 24 hours prior to PET/MRI image collection, a low carbohydrate diet is to be followed, and strenuous exercise is to be avoided. These activities are to be recorded on the provided diet and activity sheet (see Appendix C).

On the day of PET/MRI imaging, participants are advised to wear warm clothing and arrive fasted for 6 hours prior (water is permitted, and good hydration encouraged). Participants will arrive to HIRF where the MRI checklist and diet and activity checklist will be reviewed. A peripheral intravenous cannula will be inserted for radiotracer administration. A bedside blood glucose measurement will be measured if there is clinical suspicion of a blood glucose abnormality.

Whole body PET/MRI imaging will be performed on the Biograph mMR PET/MRI system after the intravenous infusion of the radiotracer  $^{18}\text{F}$  FDG. Dynamic tracer uptake will be recorded over a 45-60 minute period from the abdomen for quantitative measurement of FDG uptake in the spleen. Participants will be offered a short break, followed by collection of static images of the whole body and brain, over an estimated 30 minute period.

Dedicated brain imaging will take place using the MAGNETOM Prisma 3T MRI system. This includes MP2RAGE, T2FLAIR and diffusion weighted MRI sequences of the brain for assessment of the effects of very subtle oedema and inflammatory responses. The estimated time of image acquisition is 45 minutes per patient. Depending on initial results, there may be changes to MRI sequences to improve data collection. Participant activities or exposures will not be affected by any technical imaging sequence change.

Following image acquisition participants will be allowed food and drink and encouraged to drink water. A light meal will be provided prior to exit from HIRF. Each HIRF visit is approximately 4 hours in total duration.

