### 3.1 Study Flow Chart

|                                                 | Screening Visit | Within one week prior to MAIN study inoculation | MAIN study one to two days prior to confinement |
|-------------------------------------------------|-----------------|-------------------------------------------------|-------------------------------------------------|
| Patient Information and Informed Consent | X               |                                                 |                                                 |
| Review of MRI checklist                  | X               | X                                               | X                                               |
| Review of diet and activity sheet        | X               | X                                               | X                                               |
| Whole body PET/MRI                       |                 | X                                               | X                                               |
| Dedicated brain MRI                      |                 | X                                               | X                                               |
|                                                 |                 |                                                 |                                                 |
| Fasted blood glucose measurement         | X               | X*                                              | X*                                              |

\*If clinical concerns

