#### **4.2.2 Exclusion Criteria**

An individual who meets any of the following criteria will be excluded from participation in the study:

- Known allergic reactions to components of the study radiotracer  $^{18}\text{F}$  FDG
- Fasted screening blood glucose elevated above the normal range (BSL >6.0mmol/L)
- Failure to meet/provide the standard MRI checklist requirements
- Claustrophobia precluding image acquisition
- Significant previous radiation exposure as defined (lifetime exposure):
  - Any fluoroscopic imaging (e.g. coronary angiography)
  - Any nuclear medicine imaging (e.g. myocardial perfusion scan)
  - Greater than one previous CT scan
  - *Note:* previous plain film X-Rays and mammography are acceptable
- All other criteria as outlined in MAIN study

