#### **6.2 Enrollment/Baseline**

Baseline fasted blood glucose and MRI checklist must be completed. Low carbohydrate diet options will be discussed.

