# **7. STUDY PROCEDURES AND EVALUATIONS**

## **7.1 Study Procedures**

Medical history, medication history, physical examination and biological specimen collection as per MAIN study.

EXPLORATORY STUDY specific procedures include:

Screening visit:

- Completion of MRI checklist at screening visit – consultation between participant and study doctor
- Recording of radiation exposure history at screening visit – consultation between participant and study doctor
  - radiology including plain films, CT scans, mammography, fluoroscopy and nuclear medicine (both diagnostic and interventional).
- Participant education regarding preparation for PET/MRI imaging
  - Low carbohydrate diet advice and information sheet
  - Discussion of physical activity limitation in pre-imaging period

Attendance for imaging:

- Insertion of peripheral intravenous cannula (as per MAIN study) for blood collection and radiotracer administration
- Capillary blood glucose measurement if clinical concerns
- Urine pregnancy testing for female participants of child bearing potential if not performed as part of MAIN study protocol within 24 hours prior.
- Whole body PET/MRI imaging
  - abstinence from physical activity for >24 hours prior recorded (or type of activity recorded for consideration during interpretation if participant noncompliant with instruction)
  - low carbohydrate diet for >24 hours prior and fasting for roughly 6 hours prior recorded
  - insertion of a peripheral intravenous cannula
  - review of MRI checklist
  - infusion of  $^{18}\text{F}$  FDG via peripheral intravenous cannula
  - image acquisition – participant supine on scanner for duration of image collection
  - image review and reporting by specialist radiologist
  - $^{18}\text{F}$  FDG uptake quantification by Patlak model analysis by medical physicist, SUV semi-quantification of remaining regions of interest
- Dedicated MRI imaging
  - image acquisition – participant supine on scanner for duration of image collection

- image review and reporting by specialist radiologist

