## **7.2 Laboratory Procedures/Evaluations**

### **CLINICAL LABORATORY EVALUATIONS**

MAIN study fasted blood glucose measurements will be used as part of the EXPLORATORY STUDY screening process.

Bedside capillary blood glucose measurement will take place prior to PET/MRI scanning if there are clinical concerns.

Urine point of care pregnancy testing will be performed at either of QPharm or HIRF within 24 hours prior to PET/MRI imaging.

MAIN study baseline and serial safety blood tests (full blood count and biochemistry) will be used for comparison of imaging results.

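### Scan-day glucose is recorded only on clinical concern, so the data this protocol guarantees cannot separate pre/post changes in Ki and SUV from a change in plasma glucose

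*Supplement*

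**What the plan says.** Five places in the eight-participant protocol deal with glucose on imaging days, and all make it conditional.

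- Section 3, Preparation: "A bedside blood glucose measurement will be measured if there is clinical suspicion of a blood glucose abnormality".
- Section 3.1, flow chart: the glucose crosses at both imaging visits are starred, with the footnote "If clinical concerns".
- Section 7.1: "Capillary blood glucose measurement if clinical concerns".
- Section 7.2: "Bedside capillary blood glucose measurement will take place prior to PET/MRI scanning if there are clinical concerns".
- Section 2.2 iv, Potential Risks: the same condition. The purpose given is to check suitability to receive the tracer, not to quantify uptake.

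The compulsory value comes earlier. Section 6.2 states "Baseline fasted blood glucose and MRI checklist must be completed", and Section 7.2 states "MAIN study fasted blood glucose measurements will be used as part of the EXPLORATORY STUDY screening process". Sections 6.3 and 6.4 describe the two imaging visits separately and add no glucose reading. Section 3 plans no blood collections beyond those of the MAIN study.

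The primary outcomes (Section 2.2 ii) are FDG uptake values by region, compared after versus before inoculation. A secondary objective is "To describe the impact of early malaria infection on glucose metabolism". Neither Evaluation of data in Section 3 nor Section 10.2 mentions glucose, a glucose-corrected SUV, or Ki multiplied by glucose. The companion two-participant protocol carries the same scan-day condition.

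**The concern.** FDG is a glucose analogue and competes with plasma glucose for uptake. If plasma glucose differs between a participant's two scans, Ki and SUV can change although the tissue has not. The plan would read that change as an effect of infection or parasite burden.

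The design has no uninfected group to show what happens between two scans without malaria. Differences in fasting or diet might average out across participants. A shift caused by infection itself would push everyone the same way and remain in the mean paired difference. The hypothesis that uptake is proportional to biomass rests on the same unadjusted values.

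Readings taken only on suspicion would also come from a selected set of scans, so they could not support an adjustment for the whole group later. A scan-time glucose that was not recorded cannot be recovered.

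**Working it through.** The plan states no effect size, SD or power, so it has no figure to reproduce. The check asks how large a glucose-driven change could be without prompting a reading.

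**Inputs from the documents.** Up to eight participants (Sections 3 and 10.1), two scans each (Section 3), exclusion if fasted screening glucose exceeds 6.0 mmol/L (Section 4.2.2), paired t-test or Mann-Whitney U test at p < 0.05 (Section 10.2).

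**Assumptions, not in the documents.** With tissue metabolism constant, uptake is proportional to glucose^(-g), with g from 0.5 to 1. The value g = 1 follows for Ki if the metabolic rate, Ki x glucose / constant, is fixed; g = 0.5 is a weaker dependence.

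**Step 1: apparent change in uptake.** Change = (G2/G1)^(-g) - 1.

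| Glucose, scan 1 to scan 2 (mmol/L) | g = 0.5 | g = 1 |
|---|---|---|
| 5.0 to 5.5 | (1.100)^(-0.5) - 1 = -4.7% | 5.0/5.5 - 1 = -9.1% |
| 4.5 to 5.5 | (1.222)^(-0.5) - 1 = -9.5% | 4.5/5.5 - 1 = -18.2% |
| 5.5 to 4.5 | +10.6% | +22.2% |

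All these glucose values are below 6.0 mmol/L, so they need not raise clinical concern or trigger a measurement.

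**Step 2: what a shared shift could do to the test.** Take a paired t-test with n = 8, two-sided 0.05, and an SD of the paired change assumed to be 10%, 15% or 20%. The noncentrality is (shift/SD) x sqrt(8), with 7 degrees of freedom. For a 9.1% shift and an SD of 10% it is 0.91 x 2.828 = 2.57. The chance of p < 0.05 in the direction of the shift, with no tissue effect, is as follows.

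| Shared shift | SD 10% | SD 15% | SD 20% |
|---|---|---|---|
| 4.7% | 0.21 | 0.12 | 0.08 |
| 9.1% | 0.60 | 0.32 | 0.20 |

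With no shift, the chance in that one direction would be 0.025.

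**Step 3: number of readings needed.** 2 scans x 8 participants = 16 at most.

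**The case against.** The strongest reply is that the plan already controls the usual causes of glucose variation. Sections 3 and 5.1 require a 6-hour fast, a 24-hour low carbohydrate diet and no strenuous exercise before PET/MRI. Diet and activity are recorded, Section 5.3 logs non-compliance because it may affect data quality, and high fasting glucose is excluded at screening. This stands as mitigation. It reduces variation but does not measure what remains, and it does nothing about a shift caused by infection.

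A second reply is that MAIN study biochemistry will be compared with the imaging (Section 7.2) and that imaging follows site protocols (Section 13). Either might supply a nearby value. The documents shown do not say that the panel includes glucose or that it falls on the scan day. The supportable claim is therefore that this protocol does not guarantee a scan-time value. A reader might infer that scans will have none; the documents do not settle that.

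A third reply is that not every outcome is exposed. If glucose scaled all regions equally, ratios between regions within one scan would be unchanged, so relative organ burden is less affected. That is right, and the point is confined to absolute pre/post change.

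A reader might also infer that the glucose-metabolism objective cannot be met at all. Section 2.2 ii evaluates it through the uptake outcomes, so it can still be described as the plan defines it. What cannot be derived without scan-time glucose is a glucose metabolic rate, which the plan does not promise.

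Finally, the external FDG control named in the synopsis is a reference for the uptake measurement and gives no information on plasma glucose.

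**Conclusion.** The point holds for absolute pre/post changes in Ki and SUV, on the data this protocol guarantees. Modest differences in glucose below the screening limit could move apparent uptake by about 5% to 9% (5.0 to 5.5 mmol/L) or 10% to 18% (4.5 to 5.5 mmol/L).

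These sizes rest on an assumed exponent of 0.5 to 1 and on illustrative glucose values. The test probabilities also rest on an assumed SD. The documents supply none of these. It is tempting to extend the example to 4.0 to 6.0 mmol/L, which gives 33% at g = 1. Nothing in the documents supports a 2 mmol/L swing within one person between two prepared, fasted scans, and a limit on who may enter says little about change within a person.

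This is a hypothesis-generating pilot with mainly descriptive outcomes, so the gap limits interpretation and does not invalidate the study. It should still be closed: it sits in the primary comparison, Section 10.1 foresees using these data for later power calculations, and the missing variable is easy to collect.

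**What to change.** At both imaging visits, record a bedside glucose for every participant immediately before tracer administration, as an analysis variable. No eligibility limit, tracer rule or other clinical rule needs to change.

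Amend Section 2.2 iv, Section 3 (Preparation), the Section 3.1 footnote, Section 7.1 and Section 7.2 to match. Check that the Section 3 statement on blood collections still reads correctly.

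In Section 10.2, list glucose for each scan. Report Ki x glucose for the region with dynamic data (the spleen, per Section 3) and glucose-corrected SUV for each region, beside the uncorrected values, as a sensitivity analysis. Both versions are needed because a full correction over-corrects if the true exponent is below 1.

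The cost is one bedside reading per scan, at most 16 in total, plus the text edits. Bedside testing is already provided for, and Section 7.1 already places a cannula at these visits for blood collection and tracer administration.

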**Image Interpretation:**

Collected images will be reviewed and reported by specialist radiologists at HIRF/RBWH. Imaging metrics (FDG uptake and kinetic parameters) will be compared between baseline and follow up scans. Quantitative  $^{18}\text{F}$  FDG uptake will be calculated using Patlak model analysis from dynamic uptake imaging, yielding a  $K_i$  value ( $^{18}\text{F}$  FDG influx constant.) A nominated region of interest will have quantitative  $^{18}\text{F}$  FDG uptake calculated for each scan. Semi-quantitative  $^{18}\text{F}$  FDG uptake will be calculated using SUVs measured during static uptake imaging. All regions of interest will have SUVs calculated.

**Other data collection:**

Other blood samples will be collected as per the MAIN study.

**Evaluation of data:**

All data will be presented descriptively. Pre and post inoculation quantitative imaging metrics will be compared with paired T-tests or Mann-Whitney U tests. *Plasmodium spp.* groups will be compared with unpaired T-tests with consideration of T-value adjustment for population size and Mann-Whitney U tests. Any groups identified based on imaging results will be described with respect to demographic, clinical and biochemical data collected as part of the MAIN study.

### 3.1 Study Flow Chart

|                                                 | Screening Visit | Within one week prior to MAIN study inoculation | MAIN study one to two days prior to confinement |
|-------------------------------------------------|-----------------|-------------------------------------------------|-------------------------------------------------|
| Patient Information and Informed Consent | X               |                                                 |                                                 |
| Review of MRI checklist                  | X               | X                                               | X                                               |
| Review of diet and activity sheet        | X               | X                                               | X                                               |
| Whole body PET/MRI                       |                 | X                                               | X                                               |
| Dedicated brain MRI                      |                 | X                                               | X                                               |
|                                                 |                 |                                                 |                                                 |
| Fasted blood glucose measurement         | X               | X*                                              | X*                                              |

\*If clinical concerns

